Appendix: Definition of adverse events

1. **STUDY SYNOPSIS**

| **Title** | Protocol for evaluating the cardio–ankle vascular index to predict cardiovascular events in Japan: A prospective multicenter cohort study (CAVI-J) |
| --- | --- |
| **Coordinating Center** | [name], Okayama University |
| **Study Chair** | [name] |
| **Overall Objective** | An open label, international, multicenter observational registry designed to examine the benefits of cardio–ankle vascular index (CAVI) as a predictor of cardiovascular events in high-risk patients. |
| **Study Design** | An open-label multicenter observational registry. The study will be conducted in up to 50 sites in Japan. |
| **Study Cohorts** | A total of 3,000 subjects undergoing CAVI will be enrolled. |
| **Eligibility** | **Inclusion Criteria:**   1. Adult individual between 40 and 74 years of age 2. Type 2 diabetes mellitus 3. Metabolic syndrome 4. Hypertension categorized as high-risk 5. Chronic kidney disease (stage 3) 6. History of coronary artery disease or cerebral infarction   **Exclusion Criteria:**  1.Under 40 years of age or over 75 years of age  2.Ankle brachial index < 0.9  3.Chronic atrial fibrillation  4.Heart failure (NYHA class III or IV) or left ventricular dysfunction (EF below 40%)  5.Medical history of cancer and/or treatment for cancer within the last 5 years  6.Estimated glomerular filtration rate <30 ml/min/1.73m^2^  7.Chronic hemodialysis  8.Treatment with systemic steroids or immunosuppressants  9.Liver cirrhosis  10.History of PCI/CABG within 6months  11.Severe valvular stenosis or regurgitation  12.Determined as unsuitable for this study by a physician |
| **Duration of Study** | Accrual is expected to take 6 years. All subjects enrolled will be followed-up for 5 years. Total duration of the study will be 6 years. |
| **Primary Endpoint** | 1. Cardiovascular death  2. Nonfatal myocardial infarction  3. Nonfatal stroke |
| **Secondary Endpoint** | 1. All cause death  2. Angina pectoris with revascularization  3. New incidence of peripheral arterial disease (arteriosclerosis obliterans)  4. Aortic aneurysm  5. Aortic dissection  6. Heart failure with hospitalization  7. Deterioration in renal function (chronic dialysis or kidney transplantation) |
| **Sample size** | 3,000 subjects |

1. **BACKGROUND AND RATIONALE**

Atherosclerosis is a major contributor to the development of cardiovascular diseases and thus a major cause of mortality and morbidity [1]. Reflecting the aging of society and adoption of westernized lifestyles, the number of patients with cardiovascular diseases is also increasing [2]. Risk factors for cardiovascular disease consist of male sex, advanced age, hypertension, diabetes mellitus, dyslipidemia, obesity, and smoking. Patients often have several risk factors [3]; these need to be carefully managed to prevent future cardiovascular events. The availability of a simple and noninvasive indicator for monitoring would be a powerful tool for managing atherosclerotic risk factors.

The cardio-ankle vascular index (CAVI) was developed in Japan and is a blood pressure-independent index of arterial stiffness from the origin of the aorta to the ankle [4]. In recent years, it has been studied by many researchers worldwide and it is strongly anticipated that it will play a role as a predictive factor for arteriosclerotic diseases. Published studies have shown that CAVI increases in the presence of cerebrovascular disease [5], dementia [6], cardiovascular disease [7-9], nephrosclerosis [10], vasculitis [11, 12], hypertension [13], hyperlipidemia [10], and lifestyle-related diseases including diabetes mellitus [14], smoking [15], sleep apnea syndrome [16], stress [17] and obesity [18], all of which are considered risk factors for arteriosclerosis. Recently, a single center study reported a positive association between high CAVI values and incidence of cardiovascular diseases [19]. However, no long-term multicenter prospective studies of this association have yet been reported.

1. **STUDY DESIGN**

CAVI-J is a prospective multicenter cohort study with central registration in Japan. The targeted population is heterogeneous, given the clinical use of CAVI across a number of indications. As such, patients referred for clinically indicated CAVI and meet the inclusion and the exclusion criteria will include those undergoing evaluation for atherosclerotic diseases. The study is considered non-significant risk because: 1) CAVI is a non- invasive diagnostic modality; 2) this is an observational registry with no targeted downstream alteration to the clinical care pathway of the patient or additional interventions. Up to 50 medical centers from Japan will participate in the study, 3,000 subjects will be enrolled into the study. Each Center may not enroll more than 20% of the total number of subjects.

1. **STUDY OBJECTIVES**

**Primary Objective.** To examine the benefits of CAVI as a predictor of primary endpoints (cardiovascular death, nonfatal myocardial infarction, and non-fatal stroke).

**Secondary Objectives.** The secondary objectives of CAVI-J include:

1. To determine the clinical implication of CAVI in each cardiovascular event, including

a) Primary endpoints: cardiovascular death, nonfatal myocardial infarction, and nonfatal stroke

b) Secondary endpoints: all cause death, angina pectoris with revascularization, new incidence of peripheral arterial disease (arteriosclerosis obliterans), aortic aneurysm, aortic dissection, heart failure with hospitalization, Deterioration in renal function (dialysis or renal transplantation)

2) To determine the clinical implication of CAVI in different patient subgroups, including:

a) Type 2 diabetes mellitus

b) Metabolic syndrome

c) Hypertension categorized as highest-risk

d) Chronic kidney disease (stage 3)

e) History of coronary artery disease or cerebral infarction

f) Sex

g) Age

h) Physical activity

i) Alcohol consumption

j) Medication at baseline

3) To examine the association of change in CAVI over time and cardiovascular events

1. **STUDY ENDPOINTS**

**Primary Endpoint (**Definition of each event is defined in Appendix file.)

1. Cardiovascular death

2. Nonfatal myocardial infarction

3. Nonfatal stroke

**Secondary Endpoint (**Definition of each event is defined in Appendix file.)

1. All cause death

2. Angina pectoris with revascularization

3. New incidence of peripheral arterial disease (arteriosclerosis obliterans)

4. Aortic aneurysm

5. Aortic dissection

6. Heart failure with hospitalization

7. Deterioration in renal function (dialysis or renal kidney transplantation)

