**Analysis plan**

Data collection: categorical data will be presented as absolute numbers and percentages. Continuous data will be presented as mean ± standard deviation. Participants will be classified into several groups based on CAVI value. Baseline characteristics was compared among them. The effect of CAVI on each endpoint will be analyzed using the proportional hazard model. Incremental prognostic value was analyzed with likelihood ratio test, ROC (receiver operating characteristic) curve analysis, NRI (net reclassification improvement), and IDI (integrated discrimination improvement). The cutoff for CAVI against the incidence of cardiovascular events will be determined by ROC analysis.

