**Cardiovascular death**

The cause of death will be determined by the principal condition that caused the death, not the immediate mode of death. CEC members will review all available information and use their clinical expertise to adjudicate the cause of death. All deaths not attributed to the categories of cardiovascular (CV) death and not attributed to a non-CV cause are presumed CV deaths and are part of the CV mortality outcome. Death certificates or summaries, if possible, including the date of death and other relevant details, will be provided for all patients who have died. However, if a death certificate is the only information available for review in addition to the patient data in the clinical trial database, the CEC may decide not to use this information as cause of death if another etiology appears more plausible. The following definitions will be used for the adjudication of fatal cases:

Sudden cardiac death. Death that occurs unexpectedly in a previously stable patient and includes the following:

• Witnessed and instantaneous death without new or worsening symptoms

• Witnessed death within 60 minutes of the onset of new or worsening cardiac symptoms

• Witnessed death attributed to an identified arrhythmia (e.g., captured by electrocardiogram or witnessed on a monitor by either a medic or paramedic)

• Subject unsuccessfully resuscitated from cardiac arrest or successfully resuscitated from cardiac arrest that dies within 24 hours without identification of a non-cardiac etiology

• Un-witnessed death with no conclusive evidence of another, non-CV, cause of death (i.e. presumed CV death).

Sudden death attributable to acute myocardial infarction (MI) (MI type 3). Sudden death occurring up to 14 days after a documented acute MI (verified either by the diagnostic criteria outlined for acute MI or by autopsy findings showing recent MI or recent coronary thrombus) where there is no conclusive evidence of another cause of death. If death occurs before the biochemical confirmation of myocardial necrosis can be obtained, adjudication should be based on clinical presentation and ECG evidence.

Death attributable to heart failure or cardiogenic shock. Death occurring in the context of clinically worsening symptoms and/or signs of congestive heart failure (CHF) without evidence of another cause of death.

New or worsening signs and/or symptoms of CHF include any of the following:

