• New or increasing symptoms and/or signs of heart failure requiring the initiation of, or an increase in, treatment directed at heart failure or occurring in a patient already receiving maximal therapy for heart failure

• Heart failure symptoms or signs requiring continuous intravenous therapy or oxygen administration

• Confinement to bed predominantly because of heart failure symptoms

• Pulmonary edema sufficient to cause tachypnea and distress not occurring in the context of an acute MI or as the consequence of an arrhythmia occurring in the absence of worsening heart failure

• Cardiogenic shock not occurring in the context of an acute MI or as the consequence of an arrhythmia occurring in the absence of worsening heart failure

– Cardiogenic shock is defined as systolic blood pressure (SBP) <90 mmHg for more than 1 hour, ack of response to fluid resuscitation and/or heart rate correction, and judged to be secondary to cardiac dysfunction and associated with at least one of the following signs of hypoperfusion:

1. Cool, clammy skin
2. Oliguria (urine output <30 mL/hour)
3. Altered sensorium
4. Cardiac index <2.2 L/min/m^2^

Cardiogenic shock can also be defined in the presence of SBP ≥90 mmHg or for a time period <1 hour if the blood pressure measurement or time period is influenced by the presence of positive inotropic or vasopressor agents alone and/or with mechanical support <1 hour. The outcome of cardiogenic shock will be based on CEC assessment and must occur after randomization. Episodes of cardiogenic shock occurring before and continuing after randomization will not be part of the study outcome. This category will include sudden death occurring during an admission for worsening heart failure

Death attributable to stroke or cerebrovascular event. Death occurring up to 30 days after a stroke that is either attributable to the stroke or caused by a complication of the stroke.

Death attributable to other CV causes. Death must be caused by a fully documented CV event not included in the above categories (e.g. dysrhythmia, pulmonary embolism, or CV intervention). Death attributable to an MI that occurs as a direct consequence of a CV investigation/procedure/operation will be classified as death due to another CV cause.

Non-CV death

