• Type 3: Sudden unexpected cardiac death, including cardiac arrest, often with symptoms suggestive of myocardial ischemia, accompanied by presumably new ST elevation, new LBBB, or evidence of fresh thrombus in a coronary artery by angiography and/or at autopsy, with death occurring before blood samples could be obtained or before the appearance of cardiac biomarkers in the blood

• Type 4a: MI associated with PCI

• Type 4b: MI associated with stent thrombosis as documented by angiography or at autopsy

• Type 5: MI associated with CABG

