**Stroke (non-fatal)**

The rapid onset of a new persistent neurologic deficit attributed to an obstruction in cerebral blood flow and/or cerebral hemorrhage with no apparent non-vascular cause (e.g., trauma, tumor, or infection). Available neuroimaging studies must be considered to support the clinical impression and to determine if there is a demonstrable lesion compatible with an acute stroke. Strokes will be classified as ischemic, hemorrhagic, or unknown.

Diagnosis of stroke. For the diagnosis of stroke, the following four criteria should be fulfilled:

• Rapid onset of a focal/global neurological deficit with at least one of the following:

– Change in level of consciousness

– Hemiplegia

– Hemiparesis

– Numbness or sensory loss affecting one side of the body

– Dysphasia/aphasia

– Hemianopia (loss of half of the field of vision of one or both eyes)

– Other new neurological sign(s)/symptom(s) consistent with stroke

Note: If the mode of onset is uncertain, a diagnosis of stroke may be made provided that there is no plausible non-stroke cause for the clinical presentation

• Duration of a focal/global neurological deficit ≥24 hours OR <24 hours if attributable to at least one of the following therapeutic interventions:

– Pharmacologic (i.e., thrombolytic drug administration)

– Non-pharmacologic (i.e., neurointerventional procedure such as intracranial angioplasty)

or

– Available brain imaging clearly documents a new hemorrhage or infarct

or

– The neurological deficit results in death

• No other readily identifiable non-stroke cause for the clinical presentation (e.g., brain tumor, trauma, infection, hypoglycemia, peripheral lesion)

• Confirmation of the diagnosis by at least one of the following:*

– Neurology or neurosurgical specialist

– Brain imaging procedure (at least one of the followings):

1. CT scan
2. MRI scan
3. Cerebral vessel angiography

– Lumbar puncture (i.e. spinal fluid analysis diagnostic of intracranial hemorrhage)

If a stroke is reported but evidence of confirmation of the diagnosis by the methods outlined above is absent, the event will be discussed at a full CEC meeting. In such cases, the event may be adjudicated as a stroke on the basis of the clinical presentation alone, but full CEC consensus will be mandatory.

If the acute focal signs represent a worsening of a previous deficit, these signs must have either

• Persisted for more than one week

or

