**Figure S1 Competing Risk Analysis of Heart Failure-Related Hospitalization According to CAVI Tertiles**

[figure not shown]

*P* < 0.001

Cumulative incidence function curves illustrating the risk of heart failure hospitalization stratified by CAVI tertiles, with cardiovascular death treated as a competing event. A significantly higher cumulative incidence was observed in the high CAVI group (T3) (Gray’s test *P* < 0.001).

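### The component models for MI and stroke rest on nonfatal events alone: on the endpoint names fatal MIs and strokes drop out, and the CAVI hazard ratio is attenuated if case fatality rises with CAVI

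*Protocol*

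**What the plan says.** Section 4 of the protocol gives the primary objective in terms of "primary endpoints (cardiovascular death, nonfatal myocardial infarction, and non-fatal stroke"). Secondary objective 1 is "To determine the clinical implication of CAVI in each cardiovascular event, including" those same three as item a), so each becomes an endpoint in its own right. Section 14, Analysis plan, states: "The effect of CAVI on each endpoint will be analyzed using the proportional hazard model".

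The appendix section on cardiovascular death takes in the deaths from MI and stroke. For MI it lists "Sudden death occurring up to 14 days after a documented acute MI". For stroke it lists "Death occurring up to 30 days after a stroke that is either attributable to the stroke or caused by a complication of the stroke". An MI death that follows directly from a cardiovascular procedure goes to the category of other cardiovascular causes.

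Two entries under the non-fatal headings point the other way. The section Stroke (non-fatal) accepts a case where "The neurological deficit results in death" as one way to meet its duration criterion. The section Myocardial infarction (non-fatal) has every MI classified by type and includes "Type 3: Sudden unexpected cardiac death, including cardiac arrest".

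No endpoint list (synopsis, section 5, appendix table) contains fatal-or-nonfatal MI or fatal-or-nonfatal stroke. No rule says how long a patient must survive for an MI or stroke to count as nonfatal.

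**The concern.** Inside a composite the word nonfatal does no harm, because the fatal cases return through cardiovascular death. As a stand-alone endpoint it selects events by how they ended. Taken by its name, the nonfatal stroke endpoint treats a patient killed by a stroke as someone whose follow-up stopped without one, and the same applies to MI.

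Two things are at stake. Some MIs and strokes are not counted, which costs precision in models that already have few events. And if patients with stiffer arteries die more often from their MI or stroke, proportionally more events leave the high-CAVI group, so the hazard ratio falls below the one for all MIs or all strokes. A weak component result could then be read as a weak link between CAVI and stroke when part of the link lies in the fatal cases.

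**Working it through.** **Planning figure first.** Inputs from section 14, Sample size: relative risk 1.73 (CAVI >10 versus ≤10), 5-year risks 0.038 and 0.066, 2.5 patients with CAVI ≤10 for each with CAVI >10, two-sided alpha 5%, power 80%, dropout 20%.

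Freedman's formula with k = 1/2.5 = 0.4:

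- events = (1.96 + 0.84)² × (1 + k·HR)² / [k(HR − 1)²] = 7.849 × 1.692² / (0.4 × 0.73²) = 105.4
- CAVI ≤10: 105.4 / (0.038 + 0.4 × 0.066) = 1637, and 1637/0.8 = 2046
- CAVI >10: 0.4 × 1637 = 655, and 655/0.8 = 818 (819 if divided after rounding)
- total 2865, against the stated 810 + 2024 = 2834, a 1.1% difference

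The total reproduces only with 2024 as the CAVI ≤10 group and 810 as the CAVI >10 group, the reverse of the labels printed there. That is a separate matter. The 2.5:1 ratio is used below.

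**Expected strokes of any kind.** Chosen N = 3000; with 20% dropout taken as contributing no events, 2400 patients remain:

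- CAVI ≤10: 2400 × 2.5/3.5 × 0.038 = 65.1
- CAVI >10: 2400 × 1/3.5 × 0.066 = 45.3
- total 110.4

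This treats the planned cerebrovascular events as all strokes, fatal and nonfatal. That is an assumption, because section 14 does not say.

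**Effect of leaving out fatal cases.** With rare events, and fatal cases censored at the event:

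- HR(nonfatal) = HR(all) × (1 − f_high)/(1 − f_low)
- events remaining = 65.1 × (1 − f_low) + 45.3 × (1 − f_high)
- power = Φ(√(d × 0.286 × 0.714) × ln HR − 1.96), with d the number of events

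The documents give no case fatality, so f is assumed throughout:

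| Fatality, CAVI ≤10 / >10 | HR | Events | Power |
|---|---|---|---|
| all events counted | 1.73 | 110 | 74% |
| 10% / 10% | 1.73 | 99 | 69% |
| 20% / 20% | 1.73 | 88 | 64% |
| 10% / 20% | 1.73 × 0.80/0.90 = 1.54 | 95 | 47% |
| 15% / 30% | 1.73 × 0.70/0.85 = 1.42 | 87 | 32% |
| 20% / 30% | 1.73 × 0.70/0.80 = 1.51 | 84 | 40% |
| 20% / 40% | 1.73 × 0.60/0.80 = 1.30 | 79 | 18% |

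With all 3000 patients and no dropout, the count is 138 events and 83% power when all are counted, 118 and 56% at 10%/20%, and 105 and 48% at 20%/30%.

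Simulated rate ratios with fatal cases censored agree with the formula: 1.73 at 20%/20%, 1.51 at 20%/30% and 1.31 at 20%/40%. The direction follows the assumption. If fatality fell with CAVI, say 20%/10%, the factor would be 0.90/0.80 and the hazard ratio would rise to 1.95.

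The same factor applies to MI, but section 14 gives no MI risk or MI effect size, so no MI event count can be derived.

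**The definitions side by side.** Take a patient who has a stroke and dies of it on day 20. The cardiovascular-death section claims the death. The stroke section accepts the event as a stroke, under a heading that calls it non-fatal. The patient could be counted as a nonfatal stroke, as a cardiovascular death only, or as both. Likewise, a type 3 MI is by definition a death, yet it is a category under the non-fatal MI heading.

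**The case against.** A reader might infer that the protocol censors every fatal MI and stroke in the component models. It does not say so. The analysis plan is one sentence with no censoring rule, and the fatal wording under both non-fatal headings allows a different count. In addition, an MI or stroke precedes the death attributed to it, and nothing states that a time-to-first-event model would discard it. This objection stands: the loss of fatal cases follows from the endpoint names and the death definitions, not from an explicit rule.

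A reader might also infer that the component hazard ratios will be too low. The documents give no case fatality by CAVI, so attenuation is conditional, and equal fatality produces none. The nonfatal-only estimate is moreover a valid cause-specific hazard ratio for the event as named; it misleads only when relabelled as MI or stroke in general.

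Nor can one conclude that the endpoints contradict the sample-size section. It speaks of cerebrovascular events without saying whether deaths are included.

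Finally, the handling of death in component models is often left to a statistical analysis plan, which is not at hand. The supplementary heart failure analysis, "with cardiovascular death treated as a competing event", shows that analyses beyond section 14 exist. That answers a complaint about missing model detail. It does not answer the point about the endpoint list, which the protocol itself fixes and which has no fatal-or-nonfatal MI or stroke.

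**Conclusion.** The point holds in a limited form and concerns secondary objective 1a only. The primary composite is unaffected, because fatal MIs and strokes enter it through cardiovascular death.

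On the endpoint names, the MI and stroke models lose their fatal cases. If fatality is equal across CAVI groups the cost is precision alone: at an assumed 10%, one event in ten, and power of about 69% instead of 74% for stroke. If fatality rises with CAVI the hazard ratio is also attenuated, from 1.73 to 1.54 at 10% versus 20% and to 1.30 at 20% versus 40%. Every fatality figure here is an assumption, and the counts and power apply to stroke only. What does not depend on those assumptions is that the cardiovascular-death definitions and the fatal wording under the non-fatal headings do not settle how a fatal case is counted, and that a nonfatal-only hazard ratio does not describe MI or stroke as such.

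**What to change.** Keep nonfatal MI and nonfatal stroke as parts of the composite. For the component models in objective 1a, define two endpoints: time to first MI, fatal or nonfatal, and time to first stroke, fatal or nonfatal. Count the deaths the endpoint committee attributes to MI or stroke, including the procedure-related MI deaths now filed under other cardiovascular causes. Treat other deaths as competing events, and keep cardiovascular death as its own endpoint.

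In the appendix, reconcile the cardiovascular-death section with the two non-fatal sections and state when an MI or stroke counts as nonfatal.

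The cost is a sentence each in sections 4 and 14, the appendix clarification, and a flag on adjudicated deaths. The committee already assigns the cause of death, so no new patient data are needed. There are two small downsides. A death attributed to MI or stroke will count in two component models, so component totals will not add up to the composite. And sudden deaths without a documented MI will still not be classed as MI, so the MI endpoint improves but does not become complete.
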